### Secondary safety outcomes

Secondary safety outcome measures will be the incidence rate of serious adverse events and adverse events up to 24 months after enrolment.

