## Methods

### Study design

This will be a two-arm double-blind parallel group, placebo-controlled phase II randomised trial of oral doxycycline 100 mg daily for six weeks, versus placebo, for the treatment of nodding syndrome.

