### Study procedures

Potential participants will be evaluated through a pre-randomisation phase involving outpatient screening, obtaining consent and enrolment. Consented participants will undergo an inpatient assessment phase, a randomisation and treatment initiation phase, an intervention phase and finally, a follow up and outcome determination phase, Fig. 1.

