### Inpatient assessment

After eligibility is confirmed and consent obtained, the subject will be hospitalised for 1–2 weeks in Kitgum General Hospital for baseline assessments. The patients’ treatment will be updated per standard of care protocols. The clinical assessment will include a review of the pregnancy, birth and developmental history, the past medical history, a description of the progressive development of the symptoms of nodding syndrome, and the burden and types of seizures. A detailed physical assessment will also be performed including a neurologic, psychiatric and cognitive examination. The Gross Motor Function Classification System (GMFCS) and the Modified Rankin Scale will be used to describe gross motor abilities. The Mini-International Neuropsychiatric Interview for Children and Adolescents (MINI-KID) [26] will be used to document psychiatric disorders and the disorders classified per the Diagnostic Statistical Manual (DSM)-V criteria; Intellectual Disability will be assessed using the Child and Adolescent Intellectual Disability Screening Questionnaire (CAIDS-Q) [27]; nutritional status will be assessed against WHO 2000 anthropometric standards; cognitive function will be assessed using the Cogstate - a computerised cognitive testing program [28], and the quality of life (QOL) will be assessed using the Quality of Life in Childhood Epilepsy (QOLCE) questionnaire [29].

All participants not on standard of care treatments will be initiated on therapy including sodium valproate for seizures, nutritional, physical and psychological therapy as appropriate. Patients receiving current standard of care treatment but with ongoing seizures will have their doses of sodium valproate optimised to 20-35 mg/kg/day.

Five-10mls of blood will be drawn for standard of care testing (full blood count, liver and renal function tests, and HIV). We will also obtain skin snips for *O.volvulus* microfilaria density (on microscopy and Real Time [RT] PCR) and *Wolbachia* load testing. Lumbar puncture will be performed and 3-4mls of cerebrospinal fluid obtained. Aliquots of plasma, serum and cerebrospinal fluid will be stored for baseline evaluation of study specific tests.

All will have a 30-min diagnostic electroencephalographic (EEG) recording. In addition, an overnight EEG will be obtained in a convenient sample of 45 participants selected by stratified random sampling to reflect the five clinical stages of nodding syndrome [30].

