### Randomisation, allocation and treatment initiation phase

Once all pre-randomisation assessments are complete, participants will be randomised to either doxycycline or placebo with a 1:1 allocation as per a computer-generated randomisation schedule stratified by skin snip test results in to four groups; A, B, C and D. The randomisation code and stratification will be prepared by an independent statistician at a data centre at Global Health Uganda. The study pharmacy assistant will email the independent data centre with the study ID and the microscopy results of the skin snip for *O.volvulus* and the data centre statistician will allocate the participant to the study arms*.*

Eligibility criteria for randomisation are fulfilment of the enrolment criteria and the dose of sodium valproate rationalised to at least 20 mg/kg/day (maximum 35 mg/kg/day) if the patient still experiences one or more tonic clonic seizures a month. Participants reported to be unable to swallow capsules, those already enrolled (or who will enrol) into another trial, and those who withdrew consent since enrolment, will be excluded from randomisation.

The intervention drugs (doxycycline capsules [Azudox®] and placebo) will be obtained from Kampala Pharmaceutical Industries, Uganda. The active drug and the placebo will be labelled with the study code by Kampala Pharmaceutical Industries in collaboration with the independent statistician. Each Azudox capsule contains doxycycline hyclate equivalent to 100 mg of doxycycline base. In the treatment of *Onchocerca volvulus,* doxycycline is given in doses of 100-200 mg/day for 4–6 weeks [31]. We chose the lower dose of 100 mg/day since most participants will be adolescents many of who will also have wasting. With an average weight of 33 kg, we anticipate this dose will translate to ~ 3 mg/kg/day. The two interventions will be identical in the number of capsules (one) per day and timing. The drug administration procedures will also be identical. Both the caretakers and investigators will be blinded. However, in the event of medical emergency un-blinding of an individual participant to the PI or safety monitoring teams may be conducted. Otherwise, all treatment allocations will only be disclosed after the data is locked and a statistical analysis plan is in place.

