### Statistical analysis

Analysis will be by intention to treat. The analysis will compare the proportions of patients testing positive for and the levels or titres of antibodies to HNPs or leiomodin at baseline and at 24 months in both arms. Both crude (unadjusted) and adjusted effect estimates will be computed. The chi square test will be used to compare proportions of children with the different antibodies in the two arms; the Students t-test will be used for means of normally distributed data and the Mann-Whitney U test for skewed data. We will also determine the mean change or reduction in the levels or titres of the antibodies and inflammatory markers with the intervention. Time to event (e.g. to seizure resolution) will be measured from the date of randomisation using Kaplan Meyer Survival analysis and by Cox regression analysis. For the cognitive tests, in addition to classification as impaired or not (in comparison to norms determined from unaffected sibling controls in the concurrent case control study), we will also measure mean improvements in scores. The rates determined will be adjusted for age, HIV infection, weight for height z scores and corrected for multiple testing. We will examine safety (serious adverse events and adverse events) and assess compliance and the factors for poor compliance.

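### The only stated safety outcome is a 24-month rate dated from enrolment, so it is insensitive to a moderate excess of events confined to the six weeks of dosing, and its time origin precedes randomisation

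*Protocol article*

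**What the plan says.** The Secondary safety outcomes section of the protocol article consists of one outcome: "the incidence rate of serious adverse events and adverse events up to 24 months after enrolment". The Statistical analysis section adds only that safety will be examined. It names no comparison restricted to the treatment period.

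Other sections fix the timeline around that outcome:

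- Study design describes a "phase II randomised trial of oral doxycycline 100 mg daily for six weeks".
- Study procedures places enrolment in "a pre-randomisation phase involving outpatient screening, obtaining consent and enrolment", with randomisation as a later phase.
- Inpatient assessment: after consent, "the subject will be hospitalised for 1–2 weeks in Kitgum General Hospital for baseline assessments". During this stay "Lumbar puncture will be performed and 3-4mls of cerebrospinal fluid obtained", and valproate is started or optimised where needed.
- Randomisation, allocation and treatment initiation phase: "Once all pre-randomisation assessments are complete, participants will be randomised to either doxycycline or placebo with a 1:1 allocation". The same section says that "those who withdrew consent since enrolment, will be excluded from randomisation", so some enrolled patients may never have an arm.
- Statistical analysis: time-to-event outcomes are "measured from the date of randomisation".

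The sections on drug administration and the intervention phase plan home visits at weeks 2, 4 and 6, with adverse events documented at each. Later study visits are at 6, 12, 18 and 24 months, supplemented by unscheduled visits when a participant is ill.

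**The concern.** A rate over 24 months mixes six weeks on drug with about 98 weeks off it. If the drug causes extra events mainly while it is being taken, those events are set against two years of background illness in patients with a severe seizure disorder. The arms could then look alike on the one safety outcome the protocol names, although they differed while treatment was being given.

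A pooled rate can also let a later benefit offset an early harm. The trial hopes for better seizure control. If that lowered later event counts by 6/98 = 6%, it would cancel a doubled rate during dosing and bring the 24-month ratio to 1.00.

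Separately, the outcome is dated from enrolment and the time-to-event outcomes from randomisation. Taken literally, the safety count can include events that precede allocation, and patients who are never allocated.

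**Working it through.** **Inputs from the protocol:** 115 per arm; dosing 6 weeks; window 24 months = 24 × 365.25/12/7 = 104.4 weeks; 1–2 weeks in hospital between enrolment and randomisation.

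**Assumed inputs:** background rate of 0.5 to 5.2 events per person-year (the documents give none); constant recorded rate; excess confined to dosing; Poisson counts; two-sided 5% test.

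**1. The plan's own figure.** For 50% v 30% at 80% power, n = [1.96√(2 × 0.4 × 0.6) + 0.842√(0.25 + 0.21)]²/0.2² = 93 per arm. The continuity correction gives 93/4 × [1 + √(1 + 4/(93 × 0.2))]² = 103. Allowing 10% loss, 103/0.9 rounds up to 115 per arm, 230 in all. The stated size is reproduced. It was set for antibody positivity; no power is stated for safety.

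**2. Dilution.** Dosing is 6/104.4 = 5.7% of the window. The 24-month ratio is 1 + (RR − 1) × 6/104.4. On-treatment ratios of 1.5, 2, 3 and 5 become 1.03, 1.06, 1.11 and 1.23.

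**3. Effect of the enrolment origin.** Adding two pre-randomisation weeks gives 1 + 6/106.4 = 1.056 for a doubling, against 1.057 without them.

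**4. Power for a doubling.** Expected events per arm are 115 × weeks × rate. The statistic is z = ln(e₁/e₀)/√(1/e₀ + 1/e₁), and power = Φ(z − 1.96) + Φ(−z − 1.96). Worked at 1 event per person-year (52.18 weeks per year):

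- Six weeks: e₀ = 115 × 6/52.18 = 13.2, e₁ = 26.4, z = 0.693/0.337 = 2.06, power 54%.
- 24 months: e₀ = 230.0, e₁ = 230.0 + 13.2 = 243.2, z = 0.0558/0.0920 = 0.61, power 9%.

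| Assumed background per person-year | Six weeks: events | Power | 24 months: events | Power |
|---|---|---|---|---|
| 0.5 | 6.6 v 13.2 | 31% | 115.0 v 121.6 | 7% |
| 1 | 13.2 v 26.4 | 54% | 230.0 v 243.2 | 9% |
| 2 | 26.4 v 52.9 | 83% | 460.0 v 486.4 | 14% |
| 2.6 (0.05 per week) | 34.5 v 69.0 | 91% | 600.1 v 634.6 | 17% |
| 4 | 52.9 v 105.8 | 98% | 920.0 v 972.9 | 23% |
| 5.2 (0.1 per week) | 69.0 v 138.0 | >99% | 1200.1 v 1269.1 | 28% |

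For a tripling at 0.5, 1, 2 and 4 per person-year, power is 69%, 93%, 99.8% and about 100% in six weeks, against 14%, 22%, 40% and 67% over 24 months.

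**5. More active recording during dosing.** If events are recorded k times as often during dosing as later, the 24-month ratio for a doubling is (98 + 12k)/(98 + 6k): 122/110 = 1.11 for k = 2 and 146/122 = 1.20 for k = 4. Power then rises in both windows. With k = 4 and a later rate of 1 per person-year, the 24-month counts are 115 × 122/52.18 = 268.9 and 115 × 146/52.18 = 321.8, so z = 2.17 and power is 58%. The six-week counts are 52.9 v 105.8, with 98% power. The 7–28% range therefore belongs to the constant-rate case.

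**The case against.** The strongest reply is that this is one sentence in a condensed article. It excludes no on-treatment comparison, and an analysis plan may contain one. That is fair as far as it goes. But the sentence does fix the metric, the end of the window and the date it is counted from, and it is the only safety outcome stated.

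Second, 24-month safety follow-up is legitimate. The rationale involves effects that outlast dosing, and delayed harms can be seen only with long follow-up. This stands, and the 24-month comparison should stay.

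Third, safety during dosing is monitored: adverse events are documented at the home visits, and serious ones go to the monitoring board and ethics committees. This also stands. A reader might infer that on-treatment harms would go unrecorded; the protocol shows otherwise. What is missing from the stated outcome is a comparison that uses those data by arm.

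Fourth, a reader might infer that a drug-related excess vanishes. It does not. The number of excess events is unchanged, and only the ratio and the signal-to-noise fall. Large excesses, or events with almost no background, would still show. The background rates are assumed, recording is probably more active during dosing, and Poisson counts ignore clustering within patients, so the six-week powers are optimistic.

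Fifth, a reader might infer that events before randomisation bias one arm. They cannot depend on allocation, so they balance in expectation, and patients never randomised have no arm to enter. It can also be argued that the wording fixes only the end of the window, leaving the start to inference. What remains is an inconsistency of definition.

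**Conclusion.** The point holds in limited form. The stated safety outcome is a poor measure of harm during treatment, because about 94% of its window is off drug. With an excess confined to dosing, a doubling appears as about 1.06 over 24 months under constant recording, and up to about 1.2 if recording is two to four times more active during dosing. The six-week window had more power at every background rate examined. The exact powers depend on rates the protocol does not give.

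The documents do not support saying that the trial could not detect harm, that 24-month follow-up is an error, or that the enrolment date biases the comparison. The enrolment origin should be aligned with randomisation or first dose for clarity, but its numerical effect is negligible (1.057 to 1.056). The change is worth making before analysis; it does not threaten the trial's validity.

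**What to change.** Restate the safety outcome for randomised participants, counting events from first dose:

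1. Pre-specify a by-arm comparison of adverse events and serious adverse events from first dose through the week-6 visit, using the week 2, 4 and 6 visits already planned.
2. Keep first dose to 24 months as a separate long-term comparison for delayed harms.
3. List events between enrolment and first dose separately, not by arm.

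No new data are needed. The cost is a changed start date, one extra table and a second safety comparison, so the report should say which question each comparison answers.

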### Statistical analysis

Analysis will be by intention to treat. The analysis will compare the proportions of patients testing positive for and the levels or titres of antibodies to HNPs or leiomodin at baseline and at 24 months in both arms. Both crude (unadjusted) and adjusted effect estimates will be computed. The chi square test will be used to compare proportions of children with the different antibodies in the two arms; the Students t-test will be used for means of normally distributed data and the Mann-Whitney U test for skewed data. We will also determine the mean change or reduction in the levels or titres of the antibodies and inflammatory markers with the intervention. Time to event (e.g. to seizure resolution) will be measured from the date of randomisation using Kaplan Meyer Survival analysis and by Cox regression analysis. For the cognitive tests, in addition to classification as impaired or not (in comparison to norms determined from unaffected sibling controls in the concurrent case control study), we will also measure mean improvements in scores. The rates determined will be adjusted for age, HIV infection, weight for height z scores and corrected for multiple testing. We will examine safety (serious adverse events and adverse events) and assess compliance and the factors for poor compliance.

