### Participants

Participants will be children and adolescents with confirmed nodding syndrome as defined by the WHO [25] i.e. A child who has experienced head nodding on two or more occasions, observed by a trained health worker or documented on EEG, with symptom onset between the ages of three and 18 years, plus any one of 1) triggered by food or cold weather; 2) presence of other seizures or neurological abnormalities and cognitive decline; 3) clustering in space or time in the local population.

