### Pre-randomisation phase

Potential participants will be identified in specialised nodding syndrome outpatient clinics or community outreach centres. Screening, assent and informed consent procedures will be performed in the same clinics and the community outreach centres by study staff. The inclusion criteria will be patients with confirmed nodding syndrome as defined by the WHO [25] and aged 8 years or older. Females with a positive urinary HCG (pregnancy) test (tested if the participant has experienced menarche), those anticipated to migrate away from the study catchment area, those with known hypersensitivity to tetracyclines, and those with suspected high likelihood of non-compliance to the study drug or follow-up schedule will be excluded. Patients on phenobarbitone, carbamazepine, or phenytoin will first be weaned off and put on sodium valproate, the standard of care antiepileptic drug, before enrolment.

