#### Secondary efficacy outcomes

Key secondary efficacy measures at 24 months will include:Mean change in serum levels or titres of antibodies to HNPs or leiomodin and serum levels or titres of inflammatory markers.Mean change in dermal microfilaria density on real time PCR at 24 months.The proportions of patients achieving seizure freedom (≥1 month without head nodding or convulsive seizures), mean change in Cogstate scores, the proportions of patients with inter ictal epileptiform discharges on diagnostic EEG, proportion of participants with Gross Motor Function Classification System (GMFCS) scores 3–5; and the proportion of participants with mental health disorders on the MINI-KID and intellectual disability on the CAIDS-Q and the proportion of participants with improved Quality of Life.Others will be mean changes in weight-for-age, height-for-age (stunting), and height-for-weight (wasting) Z-scores and proportions of participants with wasting and stunting (Z-scores <− 3 SD)Incidence rate of non-nodding syndrome sick clinic visits and all cause sick clinic visits; incidence rate of all-cause hospital admissions and all-cause mortality

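### Time to seizure resolution is counted from randomisation with no requirement of seizures at baseline, so participants already seizure-free would add early events in both arms, and baseline seizure status is not among the covariates

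*Protocol article*

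**What the plan says.** All places are in the protocol article.

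- **Pre-randomisation phase:** "The inclusion criteria will be patients with confirmed nodding syndrome as defined by the WHO [25] and aged 8 years or older". No current or minimum seizure frequency is asked for.
- **Participants:** the case definition is a history: "A child who has experienced head nodding on two or more occasions". It has no recency condition.
- **Inpatient assessment:** the burden and types of seizures are recorded at baseline. Active seizures are treated as a subset of those on treatment: "Patients receiving current standard of care treatment but with ongoing seizures will have their doses" of valproate optimised.
- **Randomisation, allocation and treatment initiation phase:** a valproate dose condition applies "if the patient still experiences one or more tonic clonic seizures a month". Randomisation is stratified by skin snip result only.
- **Secondary efficacy outcomes:** the key secondary measures include the "proportions of patients achieving seizure freedom", defined as at least one month with neither head nodding nor convulsive seizures. The definition carries no condition on baseline status.
- **Statistical analysis:** analysis is by intention to treat. "Time to event (e.g. to seizure resolution) will be measured from the date of randomisation using Kaplan Meyer Survival analysis", and also by Cox regression. The adjustment variables named are age, HIV infection and weight-for-height z score.
- **Interim analyses and criteria for termination of the trial:** seizure control is the secondary outcome singled out as the reason for the added 12-month look, at which the trial may be stopped.

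**The concern.** A participant who has had no head nodding or convulsion for a month before randomisation has nothing to resolve. With time zero at randomisation and a one-month definition of freedom, such a participant becomes an event as soon as the definition can be applied, in either arm. These events say nothing about doxycycline. They enter the Kaplan-Meier curves and the Cox model at the start, bring the curves together and move the hazard ratio toward 1.

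Seizure status before treatment is likely to predict seizure status afterwards. Leaving it out of both the stratification and the named covariates gives up precision on every seizure outcome, although the data are already collected. The practical risk is that a real benefit on seizures is missed, including at the 12-month look that was added so as not to miss one.

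**Working it through.** **Inputs from the article.** 115 per arm, 10% loss, 50% v 30% antibody positivity, 80% power, 5% significance (two-sided assumed). There is no sample size or power statement for any seizure outcome.

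**Inputs assumed, because the article does not give them.** The share already seizure-free at randomisation, s: range 0 to 50%. Resolution by 24 months among those with active seizures: 50% doxycycline v 30% placebo. These rates are for illustration and have no support in the article as seizure rates.

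**1. The article's own sample size.** With p = 0.5 and 0.3 (mean 0.4):

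n = [1.96·√(2·0.4·0.6) + 0.8416·√(0.25 + 0.21)]² / 0.20² = (1.358 + 0.571)² / 0.04 = 93 per arm.

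The continuity correction gives (93/4)·[1 + √(1 + 4/(93·0.20))]² = 103. Then 103/0.9 = 114.4, rounded up to 115 per arm, total 230. The stated figure reproduces. It concerns the antibody outcome; 103 evaluable per arm is carried forward only as the number available.

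**2. Time to resolution.** Constant hazards of −ln(0.7)/24 and −ln(0.5)/24 per month give a true hazard ratio of 0.693/0.357 = 1.94 (above 1 favours doxycycline). Participants already free were counted as events at one month in both arms. Cox model, Breslow ties, 400 simulated trials per row:

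| s | HR, all randomised | Power | HR, active at baseline | Power |
|---|---|---|---|---|
| 0% | 1.96 | 85% | 1.96 | 85% |
| 10% | 1.70 | 71% | 1.97 | 79% |
| 20% | 1.52 | 53% | 1.95 | 73% |
| 30% | 1.38 | 40% | 2.00 | 71% |
| 50% | 1.21 | 14% | 1.96 | 51% |

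The reason is visible in the event counts. At s = 30%, about 0.3·206 = 62 events come from participants already free, against 72·(0.5 + 0.3) = 58 from those with seizures to resolve.

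**3. The 24-month proportion, for contrast.** Let f₁ and f₀ be the 24-month seizure-free rates among those free at entry. The pooled difference is s(f₁ − f₀) + (1 − s)·0.20. Power is Φ[(Δ − 1.96·√(2p̄q̄/n)) / √((p₁q₁ + p₀q₀)/n)], with n = 103 for all randomised and 103(1 − s) for those active at baseline. With no dilution it is 84%.

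| Rates among those free at entry | Quantity | s = 20% | s = 30% | s = 40% |
|---|---|---|---|---|
| 80% v 80% (no effect on relapse) | Pooled difference | 16 points | 14 points | 12 points |
| | Power, all randomised | 63% | 52% | 41% |
| 85% v 70% | Power, all randomised | 78% | 76% | 74% |
| 90% v 70% | Pooled difference | 20 points | 20 points | 20 points |
| | Power, all randomised | about 82% | about 82% | about 82% |
| Any | Power, active at baseline only | 75% | 69% | 62% |

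Which analysis of the proportion has more power therefore depends on whether treatment also prevents relapse, which the article does not settle. Under the 80% v 80% assumption, adding baseline seizure-free status as a covariate in the all-randomised analysis raised simulated power by about 7 points.

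**The case against.** The strongest reply is that the article is silent rather than wrong. Seizure resolution appears only as an example in one general sentence, the event is not defined there, and an unseen analysis plan may set the risk set. That is fair as far as it goes. But the article does fix the population, the time origin, the one-month definition and a list of covariates. Followed as written, these produce the problem. It is also unclear whether the covariate sentence, which follows the cognitive tests, governs the Cox model; either way, baseline seizure status is not named.

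Several stronger readings are tempting and are not supported:

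- **That the article shows some participants will be seizure-free at entry.** It shows only that this is possible. The randomisation condition concerns tonic clonic seizures, and someone without them may still have head nodding. The share appears nowhere.
- **That the 24-month proportion is biased.** It is not. Someone free at entry can relapse, so comparing all randomised participants is a proper intention-to-treat comparison.
- **That the power loss for that proportion is established.** It rests on no treatment effect on relapse, and it disappears under 90% v 70%.
- **That the dilution could cause a false early stop.** It works the other way: it makes the interim threshold of p < 0.001 harder to reach. Chance imbalance in baseline status is already covered by the test's error rate.

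One further point stands against the remedy. The month before randomisation overlaps the 1–2 week admission, when valproate is optimised, so some participants classed as active may resolve for that reason in both arms.

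**Conclusion.** The point holds for time to seizure resolution and for the covariate list. If any randomised participants are already seizure-free, and resolution is judged by the one-month definition, the analysis as written adds early events unrelated to treatment in both arms and pulls the hazard ratio toward 1. Only the possibility and the direction follow from the article. The size depends on an unknown share: under the illustrative 50% v 30%, the hazard ratio falls to about 1.70 at a 10% share, 1.38 at 30% and 1.21 at 50%.

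For the 24-month proportion the finding is narrower: the comparison is valid, and what is lost without baseline adjustment is precision. The outcome is secondary, but it is listed among the key ones and motivates the 12-month look, so the change is worth making.

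**What to change.** Before unblinding, state in the analysis plan:

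1. Time to seizure resolution is analysed in participants with at least one head-nodding or convulsive seizure in the month before randomisation. The set is defined at baseline, so the randomised comparison is preserved.
2. The proportion seizure-free at 24 months stays in all randomised participants as the main analysis.
3. Baseline seizure-free status is added to the covariates for that proportion.

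The cost is wording, since seizure burden is already recorded at the inpatient assessment. The time-to-event analysis will have fewer participants, though those removed carry no information on resolution. Resolution due to valproate optimisation around admission may still occur in both arms; the restriction does not remove it.

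### Weight-for-height Z-score is both the wasting outcome and an adjustment covariate in a mostly adolescent cohort, where it may be undefined for participants of average weight; BMI-for-age suits these ages better

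*Protocol article*

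**What the plan says.** All references are to the protocol article.

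- **Covariate.** Statistical analysis: "The rates determined will be adjusted for age, HIV infection, weight for height z scores and corrected for multiple testing". The same section plans both crude and adjusted effect estimates.
- **Outcomes.** Secondary efficacy outcomes lists, among the lower-order measures, mean changes in weight-for-age, height-for-age and "height-for-weight (wasting) Z-scores and proportions of participants with wasting and stunting", with the cut-off at a Z-score below −3 SD. The wasting index is named there as height against weight, the reverse of the order in Statistical analysis; the same index is evidently meant.
- **Reference.** Inpatient assessment: "nutritional status will be assessed against WHO 2000 anthropometric standards". No age or height range is given. BMI-for-age is not mentioned anywhere.
- **Population.** Pre-randomisation phase admits "patients with confirmed nodding syndrome as defined by the WHO [25] and aged 8 years or older", with no numerical upper age. The section on randomisation and treatment initiation expects that "most participants will be adolescents many of who will also have wasting" and works "With an average weight of 33 kg".
- **Timing.** Outcome testing is repeated at 24 months (Follow period and study outcome determination).

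**The concern.** A weight-for-height chart describes weight at a given height without regard to age. That works in young children. In adolescence, weight at a given height also depends on age and puberty, so such charts are built for young children and stop at a height limit. Above that limit the Z-score does not exist. It is undefined rather than unobserved, so there is no true value to impute.

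Two things are at stake:

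- **The wasting outcome.** Mean change and the proportion wasted could be calculated only for participants short enough to be on the chart. In this cohort those are the younger and more stunted ones.
- **The adjusted estimates.** A regression that drops participants without the covariate would report an effect for that same selected subgroup, beside a plan that declares intention-to-treat analysis.

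The choice of index is fixed in the text, so this is not a detail left to a later document.

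**Working it through.** **1. The plan's own figure.** Sample size states 230 (115 per arm) for 50% against 30%, 80% power, 5% significance (taken as two-sided) and 10% loss.

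- Uncorrected: n = [1.96·√(2·0.4·0.6) + 0.842·√(0.5·0.5 + 0.3·0.7)]² / 0.2² = 93 per arm.
- With continuity correction: (n/4)·[1 + √(1 + 4/(0.2·n))]² = 103 per arm.
- With loss: 103/0.9 = 114.4, so 115 per arm and 230 in total.

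The stated size reproduces and does not depend on any anthropometric variable.

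**2. Height implied by the mean weight.** The input from the article is 33 kg. BMI is assumed, over a range, because the article gives none. Height = √(33/BMI).

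| Assumed BMI | Height |
|---|---|
| 14 | 154 cm |
| 15 | 148 cm |
| 16 | 144 cm |
| 18 | 135 cm |
| 20 | 128 cm |

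**3. Comparison with an assumed chart limit.** The article gives no limit, so 120 to 140 cm is taken as a range. The middle column is the BMI of a 33 kg participant standing exactly at the limit, 33/height².

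| Assumed limit | BMI of 33 kg at the limit | 33 kg participant off the chart |
|---|---|---|
| 120 cm | 22.9 | at every BMI from 14 to 20 |
| 130 cm | 19.5 | at BMI 14 to 18; at BMI 20 just inside |
| 140 cm | 16.8 | at BMI 14 to 16; at BMI 18 to 20 inside, by 5 to 12 cm |

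A thin participant of average weight (BMI 14 to 16) is off the chart for every limit in the range. At a limit of 145 cm the corresponding BMI is 15.7, so thin participants of average weight would begin to fit.

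**4. Weight-for-age.** The youngest possible age at the 24-month visit is 8 + 2 = 10 years. If the weight-for-age reference ended at 10 years (assumed, not stated), the 24-month score and hence the mean change would be unavailable. If it extends further, this does not arise. Weight-for-age is an outcome only, not a covariate.

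**5. What a complete-case adjusted analysis would cost.** With 10% loss, 230 × 0.9 = 207 completers. The share without a score is assumed. Power for 50% against 30% is by the uncorrected normal approximation, which treats the adjusted analysis as a simple comparison of proportions in those left.

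| Share without a score (assumed) | Participants left | Power |
|---|---|---|
| 0% | 207 | 84% |
| 10% | 186 | 80% |
| 25% | 155 | 72% |
| 50% | 104 | 55% |
| 70% | 62 | 36% |

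The crude comparison keeps all 207 and stays at 84%.

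**The case against.** The strongest reply is that the article states no limit for its reference, so nothing in it proves that any participant is off the chart. A mean weight also gives no distribution of heights, and many participants being wasted does not mean that all are. At BMI 18 to 20 the implied height is only 128 to 135 cm, inside a chart that runs to 140 cm. This stands. A reader might infer that wasting cannot be scored at all, or that most of the 230 would be lost; the article supports neither, and the share without a score cannot be derived from it.

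A second reply is that dropping participants with a missing covariate is an assumption, and that handling of missing covariates is commonly left to the full protocol or SAP. This also stands, so the loss of power in the adjusted analysis is conditional. It does not remove the point: a rule for missing data does not supply a value that the reference leaves undefined, so the index itself has to be suitable.

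Third, a reader might infer that the intention-to-treat comparison is compromised. It is not. The chi-square comparison of antibody positivity is crude and needs no Z-score, the sample size does not involve one, and height-for-age does not use the weight-for-height chart.

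Finally, replacing the Z-score by raw BMI only for those beyond the upper age of a BMI-for-age reference would put two scales into one variable. Someone crossing that age during follow-up would then have no computable change. That objection is right, and the fix avoids it.

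**Conclusion.** The concern holds in conditional form. The article commits to weight-for-height as wasting outcome and covariate in a cohort that, by its own description, is mostly adolescent with a mean weight of 33 kg, and it does not show that the named reference covers these participants. If the chart ends between 120 and 140 cm, a thin participant of average weight, at 144 to 154 cm, is 4 to 34 cm beyond it; one with a BMI of 18 to 20, at 128 to 135 cm, is beyond it or near the limit. The wasting outcome would then be restricted to shorter, younger participants, and the adjusted estimates to a selected subgroup if the others are dropped.

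This rests on an assumed chart limit, an assumed BMI range and, for the adjusted estimates, assumed complete-case handling. Weight-for-age fails at 24 months only if its reference ends at 10 years. The effect is confined to lower-order secondary outcomes and the adjusted analysis. The change should be made because it is cheap and gives an index better suited to these ages, but the crude primary comparison does not depend on it.

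**What to change.** - In Secondary efficacy outcomes and Statistical analysis, replace weight-for-height by BMI-for-age Z-score, both as the wasting outcome and as the adjustment covariate. This also removes the reversed name of the index.
- Name the growth reference and state the ages it covers. Keep height-for-age for stunting. Keep weight-for-age only if the named reference covers the enrolled ages through the 24-month visit.
- Use one scale per analysis. For participants beyond the upper age of the BMI-for-age reference, either score BMI against the oldest reference age at both visits, or analyse change in BMI for all participants. Do not mix Z-scores with raw BMI.
- Settle this before allocation is disclosed. The article ties disclosure to data lock and a SAP being in place, so that document can carry the change.

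**Cost.** Only wording changes: weight, height and age already underlie the planned scores. Results will be less directly comparable with earlier reports that used weight-for-height. If change in raw BMI is chosen, the proportion wasted at the −3 SD cut-off still needs a reference-based score, which favours the first option.
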